***5.2 Secondary endpoints***

1. Mean Serum cholesterol and blood pressure levels, in each arm at the end of follow up

2. Cost-effectiveness of the Text Message Programme

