**Secondary Objectives**:

(i) Serum cholesterol and blood pressure levels at the end of follow up.

(iii) Cost-effectiveness of the Text Message Programme

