***4.5 Clinical and Laboratory Assessments***

Blood pressure measurements, blood for serum cholesterol and thomboxane estimation will be collected at the end of the study.

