**Blood samples**

Serum cholesterol measurements are usually routinely available in patients on lipid lowering treatment and these will be recorded at baseline. A venous blood sample, identifiable by the participants unique study number and the time and date when the sample was taken, will be collected at the 6 month follow-up visit and spun to provide serum for analysis of total cholesterol, HDL cholesterol, triglycerides and calculated LDL cholesterol.

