***4.6 Schedule of Assessment***

| **Procedure** | **Day 0a** | **Weeks**  **1-2** | **Weeks**  **3-4** | **Weeks**  **5+** | **Follow up** |
| --- | --- | --- | --- | --- | --- |
| Consent | x |  |  |  |  |
| Medical History | x |  |  |  |  |
| Blood Pressureb | x |  |  |  | x |
| Blood sample for serum Cholesterol | x† |  |  |  | x |
| Hair sample |  |  |  |  | x |
| Text message sent daily |  | x |  |  |  |
| Text message sent every alternate day |  |  | x |  |  |
| Text message sent weekly |  |  |  | x |  |
| Text message sent monthly |  |  |  |  |  |
| Extra text message if necessary |  | x | x | x |  |
| Telephone call if necessary |  | x | x | x |  |
| Questionnaire on Adherence |  |  |  |  | x |
| *Prescription refill ascertainment |  |  |  |  | x |

a: Day 0 = Day of randomisation

b: Two blood pressure readings will be performed, and the mean recorded.

† part of routine care

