***6.2. Data Analysis***

A statistical analysis of the results will be undertaken at the completion of the study. The control-adjusted differences in adherence serum cholesterol and systolic and diastolic blood pressure will be computed.

Cost-effectiveness

The direct costs of administering the TMP will be recorded, including the number of text messages sent and received, the number of telephone calls made, any time spent with GP, and any clinic contact that results. The preventive effect of any improvement in adherence to combination therapy will be estimated from data on efficacy from randomised studies and the cost-effectiveness estimated in terms of the number of life-years gained as a result of the TMP.

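### Baseline blood pressure and cholesterol have no stated role in the secondary comparison, which costs precision, and Sections 4.5 and 4.6 give different timings for blood pressure

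*Protocol*

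**What the plan says.** Outcome definition. The secondary objective in Section 2.2 is "Serum cholesterol and blood pressure levels at the end of follow up", and the endpoint in Section 5.2 is "Mean Serum cholesterol and blood pressure levels, in each arm at the end of follow up". Both refer to the final value. Neither mentions baseline.

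Analysis. Section 6.2 states: "The control-adjusted differences in adherence serum cholesterol and systolic and diastolic blood pressure will be computed". It names no model and no covariate.

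Collection of baseline values. In the schedule in Section 4.6 the blood pressure row reads "Blood Pressureb | x | | | | x", that is, Day 0 and follow-up, with the footnote "b: Two blood pressure readings will be performed, and the mean recorded". For cholesterol, the Blood samples paragraph of Section 4.5 says: "Serum cholesterol measurements are usually routinely available in patients on lipid lowering treatment and these will be recorded at baseline". The schedule agrees: it marks cholesterol at Day 0 as routine care and again at follow-up.

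Timing in the procedural text. Section 4.5 opens with: "Blood pressure measurements, blood for serum cholesterol and thomboxane estimation will be collected at the end of the study". The blood pressure paragraph that follows describes the technique but not the timing. Section 4.3, which lists what is recorded at entry, does not name blood pressure. At most it falls under the general item on cardiovascular risk factors.

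**The concern.** The protocol schedules a baseline blood pressure and collects baseline cholesterol where available, then describes a comparison in which neither has a part. The term control-adjusted refers to the control arm, not to baseline. It can be read as a difference in final means, or as the change in one arm minus the change in the other. These are different estimators with different precision, and neither is generally the most efficient.

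Precision matters here because of the job these measures are given. The abstract (Section 1.1) presents them as objective evidence of drug taking, independent of the questionnaire. The primary outcome is self-reported, and participants know whether they receive texts. The signal is also diluted: under the planning assumption of 30% against 15% non-adherence, only about 15 in 100 patients would differ in whether they stay on treatment, so any arm difference in mean blood pressure or cholesterol will be small.

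The timing conflict has a practical side. The Day 0 blood pressure rests on one cell of the schedule. A site working from the text of Section 4.5 could omit it, and a missed baseline reading cannot be recovered later.

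**Working it through.** **1. Number assessed per arm.** The protocol gives no power or precision figure for blood pressure or cholesterol. Its only sample-size figure is for non-adherence (Section 6.1): 300 patients, 80% power, 30% in controls, a 50% reduction (so 15%), 5% level, 20% loss. With mean proportion 0.225, two-sided, pooled variance under the null and no continuity correction:

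n = [1.960·√(2·0.225·0.775) + 0.842·√(0.30·0.70 + 0.15·0.85)]² / 0.15² = 121 per arm.

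Dividing by 0.80 gives 152 per arm, 304 in total. With 150 × 0.80 = 120 assessed per arm, power is 79.8%. The stated figure is therefore reproduced, and 120 per arm is the number to use below.

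**2. Variance of the arm difference.** Let σ be the SD of the 6-month value and r its correlation with baseline, with equal SDs at the two times. The documents give neither, so results are in SD units and r is an assumption, shown from 0.3 to 0.7.

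- Final means: 2σ²/n.
- ANCOVA on baseline: 2σ²/n × (1 − r²).
- Plain change score: 2σ²/n × 2(1 − r).

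**3. Detectable difference.** At 80% power, two-sided 5%, final means: (1.960 + 0.842) × √(2/120) = 0.362 SD. ANCOVA multiplies this by √(1 − r²).

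| r (assumed) | ANCOVA variance ratio | Cut in variance | Equivalent n per arm (120 / ratio) | Detectable difference, ANCOVA | Change-score variance ratio |
|---|---|---|---|---|---|
| 0.3 | 0.91 | 9% | 132 | 0.345 SD | 1.40 |
| 0.5 | 0.75 | 25% | 160 | 0.313 SD | 1.00 |
| 0.7 | 0.51 | 49% | 235 | 0.258 SD | 0.60 |

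The last column shows why the choice of estimator should be written down: below r = 0.5 a change score is less precise than ignoring baseline altogether, while ANCOVA gains at each correlation shown.

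**4. Incomplete baseline cholesterol.** Section 4.5 says only that routine values are usually available, and Section 3.1 admits patients who take no lipid-lowering drug. If a share f has a baseline value and the rest are kept in, the ANCOVA ratio is about 1 − f·r². With f = 0.8 (assumption) it is 0.93, 0.80 and 0.61 at r = 0.3, 0.5 and 0.7. With f = 0.6 it is 0.95, 0.85 and 0.71. The gain is smaller but remains.

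**5. Timing, side by side.** For cholesterol, the opening of Section 4.5 names the end of the study, but the same section and the schedule both provide for a baseline value, so the text can be reconciled as it stands. For blood pressure, the opening of Section 4.5 names the end of the study, the schedule names Day 0 and follow-up, and no other text places a reading at Day 0. That mismatch is real.

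**The case against.** The strongest reply is that the choice of covariates for a continuous secondary outcome is ordinary analysis-plan content, and that plan is not at hand. The endpoint in Section 5.2 says what is measured and when. A 6-month value is exactly the outcome an ANCOVA would use, and Section 6.2 does not exclude one. This stands. A reader might infer that the protocol discards its baseline data, but the text is silent rather than prohibitive.

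A reader might also infer that Section 4.5 has these measures taken solely at the end. It does not say so, and for cholesterol the same section says of the routine values that "these will be recorded at baseline". Only the blood pressure timing is in conflict.

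Further points that stand: with 1:1 randomisation the comparison of final means is unbiased; the outcomes are secondary and no power is claimed for them; baseline cholesterol comes from routine care and may be missing or vary in timing; and at r = 0.3 the gain is modest. Nor are these the sole possible check on self-report, since the schedule lists refill ascertainment if practical, and hair samples are stored for possible drug-metabolite analysis.

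The reply does not dispose of two things. The only analysis wording the protocol offers is open to two readings that differ in precision. And no later analysis plan can restore a Day 0 blood pressure that was not taken.

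**Conclusion.** The point holds as an improvement available at almost no cost, together with one wording conflict. It is not an error of validity, and the primary result is unaffected. Followed as worded, the plan supports an unbiased comparison that may be less precise than the collected data allow. Over an assumed correlation of 0.3 to 0.7, ANCOVA reduces the variance by 9% to 49%, and at 120 assessed per arm it lowers the detectable difference from 0.36 SD to between 0.35 and 0.26 SD. The gain for cholesterol is smaller if baseline values are incomplete. The direction does not depend on the assumed values; the size does, and it cannot be fixed from the protocol. The mismatch between Sections 4.5 and 4.6 on the Day 0 blood pressure rests on the text alone and needs no assumption.

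**What to change.** In Section 6.2, state that 6-month systolic and diastolic blood pressure and serum cholesterol are compared between arms by ANCOVA with the baseline value as covariate, reporting the adjusted difference with its 95% confidence interval, and that a plain change score is not used. Keep patients without a baseline cholesterol in the analysis, for example with a missing-indicator term, which is acceptable here because a value that predates randomisation cannot depend on the arm. The endpoint wording in Section 5.2 can stay, since it already names the final value.

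Reconcile the opening of Section 4.5 with the schedule in Section 4.6 on the Day 0 blood pressure, so that the covariate is in fact collected.

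The cost is about two sentences. No visit, sample or measurement is added beyond what the schedule already lists.

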**Appendix E Text 23**

**Appendix F Letter 24**

**1. INTRODUCTION**

***1.1 Abstract***

A randomised controlled trial of text message reminders will be conducted in 300 patients who are receiving combination therapy with at least one lipid lowering drug (eg. a statin) and/or one blood pressure lowering drug (eg. an ACE-inhibitor). The intervention arm will consist of a “Text Message Programme” – periodic text messages asking whether patients have taken their medication, adapted, over time in their frequency, to the responses received, coupled with telephone or clinic follow-up to resolve reasons for non-adherence. The control group will receive standard care. Non-adherence to therapy (discontinuing one or more of the starting combination) will be assessed at 6 months by questionnaire. Serum cholesterol and blood pressure measurement will be undertaken as independent, objective measures of drug use. Allowing for a 20% loss-to follow up, the study has 80% power to identify a statistically significant reduction in non-adherence of 50% in the intervention group at a 0.05 level of statistical significance.

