**3. STUDY POPULATION**

***3.1 Inclusion Criteria***

Participants will be men and women of all ages who own a mobile phone with text message capability. Patients will be on a combination of medicines (at least a lipid lowering drug and/or a blood pressure lowering drug) for cardiovascular disease preventive treatment.

It is anticipated that most patients will be on both classes of drug (since these are recommended for cardiovascular disease prevention). However patients who for some reason are only on one class (eg. they may be intolerant of all blood pressure lowering drugs) will still be eligible and non-adherence to the one class will be assessed.

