**6. STATISTICAL CONSIDERATIONS**

***6.1 Number of Participants***

The TMP is expected to reduce non-adherence by 50%. Non-adherence among patients with angiographically confirmed coronary artery disease has been reported to be at least 50%3. To be conservative we have taken the non-adherence rate in the control arm to be 30%. A study of 300 participants would have 80% power to detect a 50% reduction in non-adherence at the 5% level of significance. This allows for a 20% loss-to-follow up.

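### Cholesterol and blood pressure are meant as objective checks on drug use, but the arms are compared with no restriction to patients on the relevant drug class at randomisation

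*Protocol*

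**What the plan says.** Section 1.1 (Abstract) says that cholesterol and blood pressure will be measured as "independent, objective measures of drug use". Section 5.2 makes the first secondary endpoint "Mean Serum cholesterol and blood pressure levels, in each arm at the end of follow up". Section 6.2 gives the analysis: "The control-adjusted differences in adherence serum cholesterol and systolic and diastolic blood pressure will be computed". Neither section ties a marker to patients prescribed the class of drug that acts on it.

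Section 3.1 expects most patients to be on both classes but keeps eligible those "patients who for some reason are only on one class", and says that adherence to that one class will be assessed. The notes under section 5.1 follow this through for the primary endpoint. A patient who started on two classes must still be on both, a patient who started on one is judged on that one, and a switch within a class counts as adherent.

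**The concern.** A patient not on a lipid-lowering drug at randomisation has no such drug to stop, so that patient's cholesterol says nothing about adherence to one. The same holds for blood pressure. The primary endpoint adapts to one-class patients and the marker endpoint does not, although both describe adherence in the same trial population.

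The markers carry weight. Both primary endpoints come from the patient's own answers (section 4.5), and patients know whether they receive texts asking about their medication. Section 1.2 itself faults earlier studies for relying on refill data and self-report. No other objective measure of these two classes is a committed endpoint. Refill ascertainment is marked as a possible extra if practical (section 4.6), hair is stored for possible later analysis (section 4.5), and thromboxane is collected but not listed as an endpoint. Signal lost from the markers makes it harder to corroborate a self-reported benefit.

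**Working it through.** **The plan's own figure.** Section 6.1 states: "A study of 300 participants would have 80% power to detect a 50% reduction in non-adherence at the 5% level of significance". The inputs are 30% against 15% non-adherence, 20% loss and 1:1 allocation. Sidedness is not stated; two-sided is taken here. Without continuity correction this needs 121 per arm, or 242 in total, and 242 / 0.8 = 303 after rounding up. With 300 enrolled, 120 per arm are evaluable and power is 79.8%. The stated figure reproduces. It concerns the primary endpoint; none is given for the markers.

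**Attenuation.** Let p be the share not on the relevant class at randomisation and d the mean difference between arms among those on it. Assume equal variance and no effect off class.

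- All patients: the expected difference is (1 − p)d on n patients, so the expected test statistic is proportional to (1 − p)d√n.
- On-class patients only: the expected difference is d on (1 − p)n patients, so the statistic is proportional to d√((1 − p)n).
- Ratio, restricted to all: 1/√(1 − p). In terms of sample size this is worth a factor of 1/(1 − p).

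| p (assumed) | Difference kept | 1/√(1 − p) | Rise in expected statistic | Equivalent extra patients |
|---|---|---|---|---|
| 5% | 95% | 1.026 | 3% | 5% |
| 10% | 90% | 1.054 | 5% | 11% |
| 20% | 80% | 1.118 | 12% | 25% |

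**Limit on p.** Every participant is on at least one class. The share off lipid-lowering drugs plus the share off blood-pressure-lowering drugs therefore equals the share on one class. Section 3.1 expects most patients on both; if that means more than half, the two shares sum to under 50%. Having 20% off class for both markers (sum 40%) fits. Having 30% for both (sum 60%) does not.

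**Illustration of power.** Let D be the difference in a marker between taking and not taking the drug. The protocol gives no D or standard deviation, so both are assumed. The 15-point adherence difference is applied to each class, so d = 0.15 × D. This may be generous, because a two-class patient counts as non-adherent after stopping either class. There are 120 evaluable per arm, or 120(1 − p) after restriction.

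| D | p = 0 | p = 5%, all vs restricted | p = 10% | p = 20% |
|---|---|---|---|---|
| 1.2 SD | 29% | 26% vs 27% | 24% vs 26% | 20% vs 24% |
| 1.5 SD | 41% | 38% vs 40% | 35% vs 38% | 29% vs 34% |

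For a smaller effect, such as 10 mmHg on a standard deviation of 17 (about 0.59 SD), power is 10% at p = 0, and 8% against 9% at p = 20%.

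**The case against.** The best defence is that sections 5.2 and 6.2 state no analysis population, so an all-patient analysis is read from silence. A statistical analysis plan, not among the documents at hand, could restrict each marker by class without contradicting the protocol. That is fair as far as it goes. But the endpoint as worded is a mean per arm, the primary endpoint is tied to the starting class in the protocol itself, and followed as written the marker endpoint is not.

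The second defence is size. With most patients on both classes the gain is modest, and in the illustration power is low even with everyone on class. That stands: restriction removes a small avoidable loss and does not make the markers well powered.

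A reader might also infer more than the documents support:

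- **That the all-patient difference is biased or invalid.** It is an unbiased estimate of the programme's effect on mean levels in the enrolled population. It is attenuated only as a measure of the effect among patients on the class.
- **That one-class patients were never prescribed the other class.** The example in section 3.1 is intolerance, so all that can be said is that they are not on it at entry.
- **That the loss could be large for both markers at once.** The limit on p rules out 30% off class for both.
- **That no other objective information could exist.** Refill and hair data may become available; they are not committed endpoints.

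**Conclusion.** The point holds as an inexpensive improvement, not as an error that invalidates the analysis. The protocol gives the markers the job of checking drug use and admits patients for whom one marker cannot do that job. It does not align the marker comparison with starting class as it does the primary endpoint. The direction follows from the protocol's text. The size rests on assumptions: with 5% to 20% off class per marker, equal variance and no effect off class, the all-patient difference keeps 95% to 80% of the on-class difference, and restriction raises the expected test statistic by about 3% to 12%. Low power for the markers is probably the larger limitation and may remain after the change.

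**What to change.** In sections 5.2 and 6.2, make the cholesterol comparison in patients on a lipid-lowering drug at randomisation and the blood pressure comparison in patients on a blood-pressure-lowering drug at randomisation. Analyse by allocated arm, whether or not the patient still takes the drug. Class at randomisation is a baseline characteristic, so the comparison stays randomised. Keep the all-patient comparison as supplementary.

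The cost is wording, plus a record of starting class at Day 0. The notes to section 5.1 already need that record, but section 4.3 does not name it among the baseline items and should. The downside is a slightly smaller sample for each comparison.

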**6. STATISTICAL CONSIDERATIONS**

***6.1 Number of Participants***

The TMP is expected to reduce non-adherence by 50%. Non-adherence among patients with angiographically confirmed coronary artery disease has been reported to be at least 50%3. To be conservative we have taken the non-adherence rate in the control arm to be 30%. A study of 300 participants would have 80% power to detect a 50% reduction in non-adherence at the 5% level of significance. This allows for a 20% loss-to-follow up.

***6.2. Data Analysis***

A statistical analysis of the results will be undertaken at the completion of the study. The control-adjusted differences in adherence serum cholesterol and systolic and diastolic blood pressure will be computed.

Cost-effectiveness

The direct costs of administering the TMP will be recorded, including the number of text messages sent and received, the number of telephone calls made, any time spent with GP, and any clinic contact that results. The preventive effect of any improvement in adherence to combination therapy will be estimated from data on efficacy from randomised studies and the cost-effectiveness estimated in terms of the number of life-years gained as a result of the TMP.

***6.3. Data access and security***

All records will be kept securely and confidentially and analyses for reports and publications will present anonymous details. The Wolfson Institute of Preventive Medicine is part of Barts and The London Queen Mary’s School of Medicine, University of London which is registered under the Data Protection Act. In the Wolfson Institute there are two levels of security: (i) the data will be coded and kept on a network fileserver to which access is available only to a limited number of authorised users; (ii) user permissions ensure that even when logged on to the server the database is invisible to all but specifically authorised users. The server is behind a “firewall” which isolates it from the rest of the College network. It is physically protected in a locked room to which only computer staff have access, backed up every evening. Access to the building is controlled.

**7. Data Handling & Record Keeping**

***7.1 Confidentiality***

The Investigators will ensure that patient anonymity is protected and maintained. They will ensure that their identities are protected from any unauthorized parties. Information with regards to study patients will be kept confidential and managed in accordance with the Data Protection Act, NHS Caldicott Guardian, The Research Governance Framework for Health and Social Care and Research Ethics Committee Approval. All participant identifiable information will be anonymised with regard to any report or publication relating to this study.

The same standard will be followed if any patient information needs to be sent to a third party (including correspondence/communication to central laboratories, text message service administrators, or sponsor).

